### **Communication of study results to the participants**

As soon as final results of the study are available, they will be presented, both orally and in writing, to:

- The investigators;
- The national authorities;
- The participants.

A series of documents (written detailed report, and short summary) will be released to help investigators, national authorities and participants to understand the results of the study. Participants may be invited to attend a meeting during which the results will be presented and explained orally.

### **Permanent study treatment discontinuation**

Reasons for permanent discontinuation of study treatment include:

- Willingness of the patient;
- Any medical event requiring discontinuation of the study treatment (drug-intolerance or occurrence of Serious Adverse Events (SAE), occurrence or worsening of a concomitant illness);
- Need for the patient to be treated with a non-authorized concomitant medication;
- Death of the patient;
- Non-adherence to the study treatment endangering the patient's health.

If a patient wishes to discontinue study treatment at any moment, investigators should explain the importance of remaining on study follow-up, or - failing this - of allowing routine follow-up data to be used for study purposes.

A premature discontinuation of study treatment must be notified by e-mail to the clinical study manager of the CTU as soon as the investigator is aware and reported in the patient CRF. The reasons and date of the discontinuation should be documented in the patient's medical file. Study treatment discontinuation should not lead to patient withdrawal from the study: patients discontinuing their study regimen have to be followed-up according to the scheduled study visits until the end of the study and all data should be collected (under the condition that informed consent has not been withdrawn). They should receive the best possible care given their health status and current best knowledge.

## **Withdrawal of consent and loss to follow-up**

### **Consent withdrawal**

A patient will be considered to have *withdrawn consent* if s/he no longer wishes to remain in the study. In this case, a “*withdrawal of consent form*” must be filled out.

### **Loss to follow-up**

When a patient who has not explicitly withdrawn consent does not show up for routine visits, the study team (nurses, counsellors...) will search for him/her by all the way available (phone call, mailing, home-based care team). The study team will contact the patient via phone call or home visit, as long as s/he consented to phone calls and/or home visits in the consent form and provided a phone number and/or home address during the study.

A patient who does not show up for a given scheduled visit will be considered lost-to-follow-up when his/her last contact with the study team (either at the clinic, via telephone, or at home) was recorded prior to the date of his/her last scheduled visit to the clinic as per the study protocol.

## **Cost-effectiveness analysis**

The objective of the cost-effectiveness analysis in this project is to evaluate the individual and societal benefit of a mobile HCV testing service strategy compared to a communication strategy to motivate people for being tested in health centers. The cost-effectiveness analysis aims the comparison of two different public health combined-testing strategies, which raises important methodological challenges. In order to reduce the impact of assumptions of the model on both the results and the conclusions, a special attention will be paid to the collection of the price of DAAs, the analysis perspective, the time horizon and the characteristics of other HCV-related diseases. Our analyses will also account for other costs such as non-medical costs (wage loss, transportation costs, etc.).

For the cost-effectiveness analysis, the following costs will be estimated

### **Costs specific to each arm**

#### **Arm 1: Facility-based screening intervention**

- Costs of providing information in the community, time spent/person, salary/person
- Cost of HCV RDTs
- Costs of blood sample: human resources and material needed for

- Cost of blood samples conditioning and transfer between facilities, the Provincial hospital and Phnom Penh: per unit

Arm 2: Community-based screening intervention

- Costs of CHWs mobilization: time spent/person, salary/person
- Cost of HCV RDTs
- Costs of blood samples on DBS: human resources and material needed for
- Cost of blood samples conditioning and transfer towards Phnom Penh: per unit
- Cost of DBS analysis: per unit

**Costs to be collected irrespective of the arm per patient and during the whole follow-up**

- Complementary biological tests necessary for treatment initiation or follow-up: number of patients, type of test and patient-specific cost, human resources and inputs (i.e. for blood sampling)
- DAA treatment: number of days on treatment and cost of treatment
- Concomitant drugs used: number of days on treatment and cost of treatment
- Doctors' outpatient consultations: number of patients & cost of a consultation
- Nurses' or CHW outpatient consultations
- Inpatient care admissions: number of days per patient, cost of a day

***For cirrhotic patients:***

- Complementary biological tests and liver ultrasound: number of patients, type of test and patient-specific cost, human resources and inputs (i.e. for blood sampling)

***For non-responders:***

- Cost of HCV genotype
- Cost of genome sequencing
- Cost of Transient elastography
- Cost of human resources and inputs related to non-responders care before referral to the National hospital.

## 10. LABORATORY EVALUATIONS

### Blood samples collection and tests

Blood samples will be taken:

- (i) at screening phase, to measure HCV RDT and HCV RNA
- (ii) at DAA initiation for positive HCV RNA patients, to measure HBsAg and HIV RDT, complete blood count, serum transaminases, serum creatinine, fasting glycemia, prothrombin time, bilirubin, albumin,
- (iii) at week 4, to measure complete blood count, serum transaminases and serum creatinine,

- (iv) at week 8 and week 12, to measure serum transaminases and serum creatinine,
- (v) at week 24, to measure complete blood count, serum transaminases, serum creatinine, plasma HCV-RNA viral load;

|                                               | test     | DAA       | W4       | W8       | W12       | W24       |
|-----------------------------------------------|----------|-----------|----------|----------|-----------|-----------|
| Complete blood count: EDTA (mL)               |          | 2         | 2        |          |           | 2         |
| Biochemical analysis: Plasma, plain tube (mL) |          | 5         | 5        | 5        | 5         | 5         |
| Coagulation profile: Plasma citrate (mL)      |          | 2         |          |          |           |           |
| Plasma HCV RNA: EDTA tube (mL) or DBS         | 5        |           |          |          |           | 5         |
| Biobank: EDTA (mL)                            |          | 5         |          |          | 5         | 5         |
| Total number of tubes at each visit    | 1 | 4  | 2 | 1 | 2  | 4  |
| Quantity of blood at each visit (mL)   | 5 | 14 | 7 | 5 | 10 | 17 |

### HCV RNA viral load

In the arm 1, HCV RNA will be done using the Biocentric Generic HCV assay on plasma. Five mL of whole blood will be collected on EDTA tube. To avoid the risk of HCV RNA degradation during the transportation, whole blood tubes will be sent to Provincial Hospital laboratory first to collect plasma. Then, plasma tube will be sent to the UHS laboratory to perform HCV RNA.

In the arm 2, blood will be collected on DBS. DBS will be packaged in sealable plastic bags with a desiccant until transported to health center. In health center, packaged DBS will be kept in fridge. One time per week, the head of HC or nurse will insert bundled DBS into rip-resistant envelope and give to taxi for transportation to UHS in Phnom Penh. The HCV RNA will be eluted from DBS using DBS elution buffer (PBS, BSA 10%, Tween 0,05%) and manually extracted using the Qiamp Viral RNA Mini kit then amplifies using the Biocentric Generic HCV assay on the BioRad CFX96 thermocycler.

All the samples collected during the screening phase will be destroyed after HCV RNA completion.

### Biobank

During the therapeutic follow-up, blood samples will be collected for all patients and frozen at week 0, 12 and 24.

Biobank will be centralized at UHS, in Rodolphe Merieux laboratory and preparation of the aliquots will be done at this location. Plasma collected from each 5 mL blood sample will be divided in 2 mL of plasma frozen in 2 aliquots of 1 mL each. A specific database will be used to

register the samples. All the samples will be kept frozen for a period of 15 years after agreement of participant.

## **11. Clinical SAFETY**

### **11.1. Definition**

#### **11.1.1. Adverse Event (AE)**

Any untoward medical occurrence in a clinical trial participant, which does not necessarily have a causal relationship with the research or the study product.

An adverse events include:

- Any increase in frequency or intensity of an event or pre-existing condition
- Any condition (even if it was present before the start of the trial) detected after the subject signed the informed consent

An adverse events does not include:

- A medical or surgical procedure (only the condition that led to such a procedure is an adverse event)

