### **Consent**

If the patient accepts to be enrolled in the study, he will write his/her full names clearly, and date and sign the consent form, as will do the investigator (the nurse or the CHW). Written informed consent must be obtained before any exam related to the study. The original copy of the form will be stored in a location that is secure and inaccessible to other clinic employees. Participants may be given, if they wish, a copy of the consent form after they sign.

Consent will be collected in health centres for Arm 1 and directly in the household of participants for Arm 2.

A second specific information sheet and consent form will be used for the therapeutic phase. Consent will be collected in the provincial hospital.

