### **Liver disease assessment and treatment phase**

#### First visit in the Provincial Hospital (W0)

- Collect clinical data including:

- Socio-demographic: Gender, birth date, Ethnic origin, Profession, family situation, Level of income of the household, Contamination way, Liver diseases in the family
  - Drug abuse: Binge drinking, Alcohol dependence estimated by FACE questionnaire, Drug consumption and dependence
  - Anamnesis: Familial history of liver cancer, Personal history of liver disease, Vaccination HBV, Received Hepatitis C treatment in the past, was diagnosed as diabetics, Cardiovascular events, Current traditional medicine treatment
  - Co-morbidity: Metabolic syndrome, HIV infection, HBV infection,
  - Clinical examination: Weight, Height, BMI, Blood pressure, Proteinuria, Hepatic enlargement, Splenic enlargement, Ascites, Collateral circulation of the abdominal wall around the umbilicus, Encephalopathy, Ankle's edema, Extra hepatic signs
- Perform HIV and HBsAg RDTs
  - Collect biological samples and ask creatinine in emergency to get the result in one hour
  - Collect urine pregnancy test for women of childbearing age
  - Assess fibrosis level: APRI Score, Fibrosis-4 score (FIB-4). CHILD score for cirrhotic patients
  - Perform liver ultrasound: echostructure, Liver size, capsular contours, Liver nodules, Spleen size, Flow in the portal vein, Portosystemic shunt, Ascites
  - Explain and propose DAA treatment for non-symptomatic cirrhotic patients: dose, possible side effects, adherence
  - Give the prescription to the patient(monthly) and plan the next visit
  - Refer symptomatic cirrhotic patients to national hospital

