**11.1.5. Adverse event of special interest (AESI)**

AESI will be considered as SAEs and therefore declared as such to the promoter.

For this research, AESI include:

- Any grade 4 biological or clinical event;
- Any event leading to permanent or temporary discontinuation of the investigational medicinal product;
- Any hepatitis B virus (HBV) reactivation
- Cardiac arrhythmias

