### **Warning:**

If the pregnancy outcome fulfilled a seriousness criteria (eg: **anomaly or birth defect, fetal death, voluntary or therapeutic interruption of pregnancy, miscarriage needed a hospitalization**), the investigator has to notify it to the sponsor as an SAE.

Any AE must be reported, if it occurs for a participant, throughout the duration of the research, therefore from the moment the subject signed the informed consent and until the end of the follow-up of the participant.

SAE occurring to a subject after the treatment of that subject has ended should be reported to the sponsor if the investigator becomes aware of them, specially if related to the study drug. The investigator does not need to actively monitor subjects for adverse events once the trial has ended, unless provided otherwise in the protocol.

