## **Role**

The DSMB is a consultative board for the scientific committee and to the sponsor. Its members will provide general advice on the progress of the trial, including the rate of inclusions, the quality of follow-up, the overall rate of drug-related adverse events, changes in biological markers, the overall incidence of primary outcomes, and the number of subjects needed.

They will help to make difficult decisions that require an independent assessment while the trial is underway. Advice may be needed regarding:

- Premature discontinuation of the trial (because the rate of adverse events is high, the trial is no longer feasible, or the available data are sufficient);
- Substantial changes to the protocol that becomes necessary during the inclusion or follow-up phases, or to account for new scientific information.

The DSMB will conduct and interpret intermediate analyses, if any.

At the end of each meeting, a written report containing the DSMB's opinion will be sent to the sponsor and the members of the scientific committee.

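### The adverse-event definition, read literally, turns conditions that testing and the W0 work-up are designed to find into adverse events before any DAA dose

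*Protocol*

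**What the plan says.** Section 11.1.1 lists two inclusions under adverse events. The first covers worsening of an event or a pre-existing condition. The second is "Any condition (even if it was present before the start of the trial) detected after the subject signed the informed consent". The only exclusion given there is for medical or surgical procedures.

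The Warning in section 11.2 makes every AE reportable throughout the research, "therefore from the moment the subject signed the informed consent and until the end of the follow-up of the participant".

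Section 9, Consent, sets the order: "Written informed consent must be obtained before any exam related to the study". It also says: "A second specific information sheet and consent form will be used for the therapeutic phase". That second consent is taken at the provincial hospital. Neither 11.1.1 nor the Warning says which signature starts AE collection.

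After the first consent come the RDT and, if positive, the RNA sample. At W0 the investigator must "Perform HIV and HBsAg RDTs", draw blood, score fibrosis, examine the patient and perform a liver ultrasound. Section 8 offers DAA treatment only after this assessment, once creatinine and drug interactions have been checked.

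Section 11.1.5 lists "Any grade 4 biological or clinical event" among the AESIs and treats AESIs as SAEs. Section 11.2 requires SAEs and AESIs to be notified within 24 hours. Neither section has an exception for findings made before treatment.

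**The concern.** This is a case-finding trial. Its testing phase looks for undiagnosed HCV infection, and its W0 visit looks for co-infection and liver disease. A definition that makes every newly detected pre-existing condition an adverse event captures what the protocol sets out to find, in people who have not yet taken a tablet and in some who never will.

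One secondary objective in section 4 is the safety of the 12-week DAA regimen. If the AE, SAE and AESI records hold prevalent disease alongside events on treatment, raw counts from them do not describe the regimen. Investigators would also owe expedited reports on grade 4 values from blood drawn before the first dose. With two consents and no rule for choosing between them, two sites could apply the definition differently.

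**Working it through.** **Step 1. What the second bullet adds.** Worsening of a pre-existing condition is already covered by the first bullet in 11.1.1. For pre-existing disease, the second bullet therefore adds conditions that have not worsened but are newly found. Those are baseline findings.

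**Step 2. Order of events (sections 8 and 9).** Screening consent, then RDT and RNA, then therapeutic-phase consent, then W0 assessment, then first DAA dose.

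**Step 3. The literal rule under each possible starting consent.**

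| Condition | First found by | Screening consent starts the clock | Therapeutic-phase consent starts the clock |
|---|---|---|---|
| HCV infection, not known before | RDT and RNA | AE | Not an AE: found earlier |
| HCV infection known before consent | Not found by the trial | Not newly detected | Not newly detected |
| HIV or HBV, not known before | W0 RDTs | AE | AE |
| Cirrhosis or HCC, not known before | W0 examination, scores, ultrasound | AE | AE |
| Abnormal W0 laboratory value | W0 blood sample | AE; AESI if grade 4 | AE; AESI if grade 4 |

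The W0 rows do not depend on the choice of consent. The HCV row does.

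**Step 4. Searching for an exemption.** The exceptions in section 11.1.3 concern only whether certain hospitalisations are SAEs. They do not remove baseline findings from the AE definition.

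**Step 5. Scale of the HCV row, if the screening consent counts.**

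- Plan's own figure (section 14): 6,000 × 0.05 = 300 antibody positive, as stated.
- Lower number tested: 60% uptake, the low end of the section 14 range, gives 8,000 × 0.60 = 4,800, and 4,800 × 0.05 = 240 antibody positive.
- RNA-to-antibody ratio, low: 262/372 = 0.704, from the ART cohort in section 3.
- RNA-to-antibody ratio, high: 5.4/6.8 = 0.794, from the survey of people living with HIV in section 3.
- Low end: 240 × 0.704 = 169.
- Middle: 300 × 0.704 = 211.
- High end: 300 × 0.794 = 238.

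Both ratios come from people with HIV; applying them to the general population is an assumption. The calculation also assumes that every antibody-positive person gets an RNA result. The range includes people whose HCV infection was already known. Their number is not given, though section 3 says that few chronically infected people know their status. The documents give no usable rates for HIV, HBV, cirrhosis, HCC or grade 4 values at W0, so those are not counted.

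**The case against.** The strongest reply is that the protocol in practice already separates baseline from treatment.

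- Section 9 records HIV and HBV infection as co-morbidity at W0 and takes a history of liver disease. It schedules AE evaluation only at W4, W8 and W12. This makes mass filing of AEs at W0 less likely, but it does not narrow the window that the Warning opens at consent.
- Section 11.2.1 asks for a causality judgement on every AE. Adverse-reaction counts are therefore largely protected. AE, SAE and AESI counts are not.
- No AE proportion is listed among the endpoints in section 7, and a statistical analysis plan could define treatment-emergent events. That stands for the analysis. It does not change what investigators must record, or report within 24 hours, under the protocol.
- The general phrase in 11.1.1 about untoward occurrences might be read to leave out the disease under study. The explicit inclusion bullet points the other way.

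Two stronger readings are tempting. A reader might infer that every RNA-positive person carries an AE before treatment. The documents do not support this: it fails if the therapeutic-phase consent starts the clock, and it fails for people whose infection was already known.

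A reader might also infer that the DSMB could be led to stop the trial by prevalent disease, because section 12.2 names a high AE rate as a possible reason. The same section says that what the DSMB follows is the overall rate of drug-related events, and infections found before the first dose do not belong there.

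**Conclusion.** The point holds as a conflict in the protocol's text. Sections 11.1.1, 11.1.5 and the Warning in 11.2 do not fit a design in which consent precedes testing and the W0 work-up precedes treatment. Whichever consent counts, newly found HIV, HBV, cirrhosis, HCC and W0 laboratory abnormalities are literal AEs before any DAA dose, and grade 4 values are AESIs. If the screening consent counts, about 169 to 238 newly found HCV infections join them, on the assumptions shown above.

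The damage is limited to the AE, SAE and AESI records behind the DAA safety objective and to the reporting load. The primary endpoint is untouched, the treatment-phase endpoints are not compared between arms, and pre-dose events can be separated at analysis if onset and first-dose dates are used. The wording should be corrected because it fixes what is collected and reported.

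**What to change.** Reconcile sections 11.1.1, 11.1.5 and the Warning in 11.2 with the consent, W0 and follow-up text in section 9:

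1. State which consent starts AE collection.
2. In 11.1.1, state that conditions first found by the protocol's own RDT and RNA tests or by the W0 assessment are recorded as baseline findings or medical history, unless they worsen afterwards or result from a study procedure such as blood sampling.
3. Summarise DAA safety on AEs, SAEs and AESIs with onset or worsening after the first dose, among patients who took at least one dose. Tabulate pre-dose findings separately. This item may sit in the statistical analysis plan.
4. The sponsor should reconcile the expedited-reporting text for grade 4 findings made before the first dose; no rule is proposed here.

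The cost is a few lines of amended wording and one comparison of onset date with first-dose date. Section 11.2.1 already refers to an onset date for each event, and section 8 requires dispensing records. The small downside is the extra table of pre-dose findings.

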#### **11.1.2. Adverse Reaction (AR)**

All untoward and unintended responses to an investigational medicinal product related to any dose administered.

#### **11.1.3. Serious Adverse Event/Reaction (SAE/SAR)**

A serious adverse event/reaction refers to any untoward medical occurrence or reaction that at any dose:

- results in death;
- is life-threatening\*;
- requires hospitalization or prolongation of existing hospitalization\*\*;
- results in persistent or significant disability or incapacity;
- is a congenital anomaly or birth defect;
- is an "important medical event" including adverse event of special interest\*\*\*

\*means that the subject was at immediate risk of death at the time of the event; it does not refer to an event which hypothetically might have caused death if it were more severe.

\*\* hospitalization is defined as admission to hospital, regardless of the length of stay, even if hospitalization is a precautionary measure allowing continued observation.

**Exceptions:**

Do not constitute a serious adverse event:

- Hospitalization for a pre-existing condition that has not worsened, scheduled before inclusion in the trial
- Hospitalization without harmful or unwanted manifestation (hospitalization for administrative or social reasons, elective hospitalization for medical or surgical treatment, hospitalization predefined by the protocol, etc.)

\*\*\*the investigator's medical opinion can decide whether an event can be qualified as serious. The following should also be considered serious: events that are not immediately life threatening or which do not result in death or hospitalization but may jeopardize the subject or may require medical or surgical intervention to prevent one of the above characteristics/consequences mentioned above. Examples: allergic bronchospasm requiring intensive treatment at an emergency room or at home, blood dyscrasias, convulsions.

